### Statistical analyses

The primary analysis will be based on the intention-to-treat principle, including all randomized patients with usable records for SpO_2_. The proportion of patients whose SpO_2_ is <90 % during at least 5 s between 30 s and 5 min after the onset of intravenous injection of the study drug in the immediate aftermath of a GTCS will be presented in each group (naloxone and placebo) with the corresponding exact 95 % CI. These proportions will be compared between the two groups using Pearson’s chi-square test (or Fisher’s exact test if conditions for the chi-square test are not fulfilled).

A per-protocol analysis of the primary endpoint will also be performed in the population, which will comprise all randomized patients with usable records for SpO_2_ having no major protocol deviation such as patients in whom the onset of intravenous injection of the study drug was within the 2 min following the end of the seizure (whereas those in whom the study drug was administered >120 s after the end of the seizure will be excluded). Secondary endpoints will be compared between groups using Pearson’s chi-square test, Fisher’s exact test, Student’s *t* test, or the Wilcoxon-Mann–Whitney test, depending on the variable studied. The significance level will be set at 0.05.

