### Study conduct

All included patients will benefit from continuous monitoring of SpO_2_ and will be have a peripheral venous catheter inserted throughout the video-EEG/video-SEEG. During video-EEG/video-SEEG, patients are continuously supervised by one or two specialized nurses during the daytime at all participating centers. This continuous supervision allows immediate intervention in case of occurrence of a seizure. In six centers, patients are supervised by one specialized nurse during the night, whereas they are not supervised in the other centers. Given this organization of some EMUs, a GTCS might occur during a period without supervision. Unsupervised GTCS will not result in randomization, and the patient will remain eligible for randomization in case of occurrence of another GTCS during the monitoring. Inclusion in the study will not modify antiepileptic drug withdrawal, the management of which will remain at the discretion of each center.

In case of occurrence of a GTCS, patients will be randomized (1:1) into one of two groups: a single dose of 1 ml of either (1) naloxone or (2) placebo will be administered by the supervising nurse or physician, using direct intravenous injection. The evolution from a focal seizure to a GTCS being gradual, and the total duration of the seizure ranging from 2 to 3 min, the injection will be prepared during the course of the seizure. Given the assumptions about the role of endogenous opioid release in the spontaneous termination of seizures, naloxone will be administrated immediately after the end of the GTCS and not before. Specifically, treatment administration will be performed within the 2 min following the end of the GTCS.

Immediately after the administration of the treatment, the supervising nurse or physician will monitor respiratory movements to detect absence of chest expansion, SpO_2_, heartbeat and blood pressure, recovery of consciousness and pain, using a visual analogue scale. In patients with SpO_2_ < 85 % during >2 min after the injection of the study drug, O_2_ will be administered using a high-concentration breathing mask (15 L/min). Occurrence of one or more GTCSs during the 2 h following treatment administration will be monitored.

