### Outcome measures

#### Primary endpoint

The primary endpoint is the proportion of patients whose SpO_2_ is <90 % during at least 5 s between 30 s and 5 min after the onset of intravenous injection of the study drug in the immediate aftermath of a GTCS. The delay between the end of the seizure and administration of the treatment will be precisely determined by the video recording of the event, given that the nurse or physician who will administer the study drug will be required to both loudly order “injection” and raise an arm at the onset of injection. Previous studies have shown that the measurement of SpO_2_ is reliable in the vast majority of seizures, including GTCSs [18, 19]. To eliminate artefactual changes of SpO_2_, however, the criterion of hypoxemia duration of at least 5 s is required.

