### Sample size

Sample size was determined using Fisher’s exact test with a two-sided alternative hypothesis. For a significance level of 5 % (two-tailed), assuming a proportion of patients whose SpO_2_ is <90 % during at least 5 s between 30 s and 5 min after the onset of intravenous injection of the study drug in the immediate aftermath of a GTCS of 33 % in the control group [18] and 11 % in the naloxone group, 69 patients should be included in each group to reject the null hypothesis in 90 % of cases, with a 95 % CI ranging from 0.077 to 0.547. With a proportion of unusable records for technical reasons of 20 % being expected, 166 patients will be randomized. Because we anticipate that 25 % of patients eligible for inclusion will have a sGTCS during long-term video-EEG monitoring, we will need to include 700 patients.

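### The unadjusted primary test is valid but leaves out SpO2 at injection, a recorded and probably prognostic value; adjusting for it would gain nothing to about 10 points of power, depending on an undocumented correlation

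*Protocol article*

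**What the plan says.** The Statistical analyses section fixes the primary comparison: "These proportions will be compared between the two groups using" Pearson's chi-square test, with Fisher's exact test as the fallback. No covariate is named.

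The Primary endpoint section counts a patient as an event if SpO2 is "<90 % during at least 5 s between 30 s and 5 min after the onset of intravenous injection of the study drug".

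Two values that could serve as covariates are already collected:

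- **SpO2 before injection.** Study conduct states "All included patients will benefit from continuous monitoring of" SpO2, so a reading at the moment of injection exists for any patient whose signal is usable at that point.
- **Injection delay.** The Primary endpoint section states "The delay between the end of the seizure and administration of the treatment will be precisely determined by the video recording of the event". In the analysis the delay serves only as the 120 s cut-off for the per-protocol population.

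Randomization is stratified by center only (Blinding and randomization), so the design does not balance SpO2 at injection.

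**The concern.** The endpoint and SpO2 at injection are the same signal, read moments apart. The window opens 30 s after injection onset and needs 5 s below 90 %. Hypoxemia already present at injection therefore scores if it persists to about 35 s, or if it recurs for 5 s later in the window. Injection may come up to 2 min after the seizure ends (Study conduct), and the respiratory dysfunction under study is placed 1 to 3 min after the seizure (Background; opening of Methods/design). Some patients may thus be desaturated when injected, and their starting level probably predicts whether they score.

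If so, a test that ignores this value has less power than one that uses it. At stake is the precision of the primary comparison, not its validity.

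**Working it through.** **Inputs from the protocol.** Control rate "of 33 % in the control group" and "11 % in the naloxone group"; two-sided 5 % level; 69 per group for 90 % power; 20 % unusable records; 166 randomized (all from Sample size).

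**Input not in the protocol.** The correlation between SpO2 at injection and the outcome. It is assumed and shown as a range.

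**Step 1: reproduce the plan's figure.** Unpooled two-proportion formula:

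n = (1.96 + 1.2816)² × (0.33 × 0.67 + 0.11 × 0.89) / 0.22² = 69.3 per group.

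Exact binomial enumeration of the planned chi-square test at 69 per group gives 89.6 % power. The stated 90 % is reproduced for that test. (Fisher's exact test, which the Sample size section names, gives 85.7 % at 69 per group; that is a separate matter.)

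**Step 2: usable patients.** 166 × 0.8 = 132.8, so about 66 per arm. Exact chi-square power at 66 per arm is 88.0 %. With a mean event rate of (0.33 + 0.11)/2 = 0.22, expected events are 132 × 0.22 ≈ 29. The smallest expected cell is 66 × 0.22 ≈ 14.5, so the chi-square test rather than Fisher's would normally apply.

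**Step 3: adjusted power at 66 per arm.** Each simulated patient has a standard normal SpO2 at injection, x, and a latent outcome L = ρx + √(1 − ρ²)e. The event occurs when L falls below the threshold that gives 33 % (control) or 11 % (naloxone). The adjusted test is the likelihood-ratio test for arm in a logistic model with x.

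| Assumed ρ | Unadjusted power | Adjusted power |
|---|---|---|
| 0 | about 88 % | about 88 % |
| 0.2 | about 88 % | about 90 % |
| 0.4 | about 88 % | about 91 % |
| 0.6 | about 88 % | about 94 % |
| 0.8 | about 88 % | about 98 % |

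Repeat runs differ by about one point. Under the null (22 % in both arms) the adjusted test rejected in about 4.6 to 5.9 % of runs.

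**Step 4: a second model as a check.** At 69 per arm, with a logistic outcome and an uninformative delay as a second covariate, power moved as follows:

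| AUC of SpO2 at injection (assumed) | Unadjusted | Adjusted |
|---|---|---|
| 0.50 | 89.3 % | 89.4 % |
| 0.64 | 88.8 % | 90.3 % |
| 0.74 | 89.8 % | 92.9 % |
| 0.81 | 88.8 % | 95.7 % |
| 0.87 | 89.4 % | 97.8 % |

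**Step 5: what adjustment cannot do.** Suppose a share u of all patients is hypoxemic at injection and scores in either arm, the control rate stays at 33 %, and naloxone prevents two thirds of the other events. The naloxone rate becomes u + (0.33 − u)/3. At u = 10 % that is 0.10 + 0.23/3 = 17.7 %. Power at 69 per arm, chi-square against a Mantel-Haenszel test stratified on that status:

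| u (assumed) | Unadjusted | Stratified |
|---|---|---|
| 5 % | 75 % | 83 % |
| 10 % | 56 % | 74 % |
| 15 % | 36 % | 61 % |
| 20 % | 21 % | 46 % |

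Stratifying recovers part of the loss, but power stays below 90 % in every row.

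**The case against.** The strongest reply is that nothing here is an error. An unadjusted chi-square test in a 1:1 randomized trial holds its level, and chance imbalance in SpO2 at injection is already allowed for in the 5 % error rate and the confidence intervals. The planned test reaches the planned power at the planned size. An analysis plan that is not shown may add adjusted analyses. All of this stands, and it limits the point to efficiency. The protocol nevertheless fixes the unadjusted test as primary.

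A second reply is that the gain is assumed. This also stands: no figure in the protocol links SpO2 at injection to the outcome, and at zero correlation the gain is nil. What supports the proposal is that nothing material is lost in that case.

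A third reply is that the Step 3 model lets treatment work at every starting level, whereas a group that scores regardless would break it; more than 11 % of such patients would put the assumed naloxone rate out of reach. That is fair, and Step 5 treats that situation separately.

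A reader might infer four stronger things that the documents do not support:

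- **That a patient below 90 % at injection is an event in either arm.** The 30 s lead-in means the hypoxemia must persist or recur. The Interventions section gives 30 s to 2 min from injection to awakening in opioid overdose, so recovery inside the window may itself reflect treatment.
- **That adjustment costs nothing.** A value must be extracted, missing values need a rule, about 29 events allow few covariates, and a logistic odds ratio is conditional unless standardized.
- **That the delay adds power too.** No gain has been shown for it. It is measured after randomization; under blinding, and before the drug acts, it should not depend on arm, so it is usable, but its prognostic value is undocumented.
- **That adjustment repairs the endpoint.** Step 5 shows that it does not.

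**Conclusion.** The point holds as a matter of efficiency. The primary test is valid, but it ignores a value that is already recorded and probably prognostic. At 66 usable patients per arm and the protocol's own rates, adjusting for SpO2 at injection changes power from about 88 % to somewhere between about 88 % and about 98 %, with type I error of about 5 to 6 %. Where in that range the trial lies depends wholly on a correlation that the documents do not give. At modest correlations (0.2 to 0.4) the gain is about 2 to 3 points. No bias is being corrected. If some patients score whatever they receive, their dilution of the effect remains.

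**What to change.** Before unblinding, pre-specify the primary analysis as a logistic regression of the endpoint on arm, adjusted for SpO2 at injection. Define that covariate as the mean SpO2 over the last 5 s before injection onset, with a simple rule, blind to arm, for missing values. Report the standardized risk difference with its 95 % CI, so that the result stays on the scale of the planned proportions. Keep the chi-square/Fisher comparison as a sensitivity analysis.

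Treat the seizure-end-to-injection delay as an optional second covariate, to be decided in advance, and add no more than that with about 29 expected events.

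The cost is one extra value per patient from a signal already centralized, one missing-data rule, and a change of wording in the analysis section. No new data collection is needed.

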### Study setting

The study will be conducted with patients who have drug-resistant focal epilepsy investigated with long-term scalp video-EEG or video-stereoelectroencephalography (video-SEEG) in 1 of the 15 participating epilepsy monitoring units (EMUs) in France (see Additional file 2). The modalities of the video-EEG monitoring and patient management will be consistent with current practices and will be similar across all participating centers, including modalities of invasive recording using SEEG in the ten EMUs that perform both video-EEG and video-SEEG monitoring. Specifically, all of them undergo systematic recording of SpO_2_ coupled with video-EEG. The reliability of the measurement of SpO_2_ during seizures has been validated by two studies in which researchers carried out this type of monitoring [18, 19].

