### Blinding and randomization

To avoid any follow-up or measurement bias, the patient, the supervising nurse, or the physician and the investigator will not be aware of the nature of the administered treatment. To respect the blinding and to ensure indistinguishability, preparations of both naloxone and placebo will be centralized by the pharmaceutical department of Hospices Civils de Lyon. The study drugs will then be distributed to the pharmacies of other investigator sites and stored at room temperature. Because of urgent need of treatment in case of occurrence of GTCS, one or more study treatments will be stored at room temperature in each EMU according to the expected number of randomizations at each center

Randomization will be centralized, stratified by center, and balanced by block of patients. For each study center, randomization lists will be prepared by the clinical research unit of Hospices Civils de Lyon. The pharmaceutical department of Hospices Civils de Lyon will prepare numbered batches according to the randomization lists.

In case of the occurrence of a GTCS, the affected patient will be randomized in a 1:1 ratio and assigned to the naloxone group or the placebo group. The batch number will be registered in the patient’s case report form. All digital data (video, EEG, respiration, SpO_2_) will be centralized and evaluated in blinded fashion with other data by the coordinator investigator of the study, who will not be involved in the video-EEG monitoring of the included patient.

If case of occurrence of a serious adverse event, the Antipoison and Toxicovigilance Center of Lyon will proceed to unblinding 24 h/24 h upon request by the study coordinator, the investigators, or the sponsor. A detailed written procedure for unblinding will be provided to all persons involved.

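### Randomization is stratified by center, but the stated primary test ignores center; the test is valid, yet conservative if hypoxemia rates differ materially between centers

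*Protocol article*

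**What the plan says.** Three sections of the protocol article bear on the point.

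- **Study setting** and **Blinding and randomization.** Patients come from "1 of the 15 participating epilepsy monitoring units (EMUs) in France". "Randomization will be centralized, stratified by center, and balanced by block of patients", and "the affected patient will be randomized in a 1:1 ratio". The block size is not given.
- **Statistical analyses.** The proportion with the primary event "will be presented in each group (naloxone and placebo) with the corresponding exact 95 % CI". Then: "These proportions will be compared between the two groups using" Pearson's chi-square test, or Fisher's exact test if the conditions for chi-square are not met. Neither test uses center.
- **Study conduct.** Withdrawal of antiepileptic drugs is not standardized: "the management of which will remain at the discretion of each center". Six centers have a nurse on duty at night and the others do not. Study setting adds that ten centers also record with SEEG, but says that monitoring and management will be alike across centers.

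**The concern.** Blocking within center keeps the arms nearly balanced in every center. Differences between centers then largely cancel out of the naloxone–placebo contrast. The pooled Pearson variance does not know this: it still counts between-center variation as noise. If centers differ, the standard error is too large for this design, the actual type I error falls below 5%, and some attainable power is not used.

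The article makes some heterogeneity conceivable. Drug withdrawal is left to each center, night staffing affects which seizures can be randomized, and SEEG is used in only some centers. The primary test is named explicitly, so this is a stated choice and not a detail left to the analysis plan. What is at stake is efficiency and consistency between design and analysis.

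**Working it through.** **Inputs from the article.** 15 centers, 1:1 allocation in blocks within center, two-sided 5%, event rates 33% (placebo) and 11% (naloxone), 69 evaluable per group, 166 randomized, 20% unusable records.

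**Assumptions.** Block size, center sizes and between-center SD on the logit scale. The article gives none of them, so ranges are shown.

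**1. The plan's own figure.** Exact enumeration at 69 per group gives 89.6% power for Pearson's test, the planned primary test. It gives 85.7% for Fisher's test, the one named under Sample size. So 90% fits the chi-square test, which is the baseline here. The difference for Fisher's test is a separate matter.

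**2. Why Pearson becomes conservative.** With perfect balance within centers, the ratio of true variance to Pearson variance under the null is

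R = 1 − Var(p_c) / [p(1 − p)],

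where p_c is the center rate and p = 0.33, so p(1 − p) = 0.2211. The true size is 2Φ(−1.96/√R). Var(p_c) is obtained by integrating a logit-normal distribution with mean 0.33:

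- SD 0.5: R = 1 − 0.0112/0.2211 = 0.950; size 4.4%
- SD 1.0: R = 1 − 0.0358/0.2211 = 0.838; size 3.2%
- SD 1.5: R = 1 − 0.0618/0.2211 = 0.721; size 2.1%

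These are limiting values. With 15 centers and incomplete blocks, simulated sizes should lie a little higher.

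**3. Simulation.** Pearson was compared with a Cochran-Mantel-Haenszel (CMH) test stratified by center, in three settings:

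- A: 138 evaluable, blocks of 2 or 4, equal or unequal centers, 20,000 runs per setting.
- B: 132 evaluable, blocks of 4, unequal centers, 6,000 runs.
- C: 166 randomized in blocks of 4, unequal centers, 20% of records then lost at random, 20,000 runs.

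| SD (logit) | Pearson size %, A / B / C | CMH size %, A / B / C | CMH power minus Pearson power (points), A / B / C |
|---|---|---|---|
| 0 | 4.7–5.1 / 4.9 / 5.1 | 4.6–5.1 / 4.8 / 4.9 | −0.8 to −0.4 / −0.5 / −1.5 |
| 0.5 | 4.5–4.9 / 4.9 / 4.9 | 4.9–5.1 / 5.3 / 5.1 | 0.0 to +0.2 / −0.2 / −0.5 |
| 1.0 | 3.3–3.6 / 4.1 / 3.8 | 4.7–5.1 / 5.3 / 5.0 | +1.3 to +1.8 / +1.5 / +1.4 |
| 1.5 | 2.4–2.6 / 3.2 / 3.0 | 4.8–5.1 / 5.0 / 4.9 | +3.1 to +3.6 / +4.2 / +3.6 |

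Monte Carlo standard error at 5%: √(0.05 × 0.95/20,000) = 0.15 points, or 0.28 points with 6,000 runs. Pearson power is 89.3–91.4% in A, 87.7–89.1% in B and 88.4–89.3% in C, and it does not decline as SD rises. Setting C shows that losing records after randomization weakens the within-center balance. That moderates the conservatism and makes the cost of stratifying slightly larger when centers are alike.

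**4. What these SDs mean.** Around a median rate of 33%, logit(0.33) = −0.708. The central 95% of center rates is the inverse logit of −0.708 ± 1.96 × SD: about 16–57% at SD 0.5, 6–78% at SD 1.0 and 3–90% at SD 1.5.

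**The case against.** The strongest reply is that the harm depends on heterogeneity that the article does not show. It gives no center-specific rates, and Study setting says that monitoring and management will be similar across centers. Every randomized seizure is a supervised one, so night staffing can change only the mix of day and night seizures, and the article does not link that mix to hypoxemia. An SD of 0.5 is already a wide spread, and there the two tests perform almost alike. All of this stands, and it limits the size of the point. It does not remove the mismatch between design and test.

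Three stronger readings are tempting, and the article does not support them.

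- **That the primary test is invalid.** Its size never rises above 5% beyond simulation error. A significant result would stand.
- **That power falls below plan because center is ignored.** Pearson power stays at about 88–91% in all settings. What is given up is a possible gain.
- **That no between-group effect estimate is planned.** Statistical analyses names only per-arm proportions with exact intervals and a test. This is a condensed article, the full protocol and analysis plan are not shown, and its silence does not exclude a risk difference or ratio with CI.

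Sparse centers are also a fair objection: 166/15 is about 11 randomized per center on average, and some will have far fewer.

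**Conclusion.** The point holds as a modest matter of efficiency and consistency. The design stratifies by center and the stated primary test does not. The direction is certain: if rates differ by center, Pearson's test is conservative and a center-stratified test is not. The size is not known, because it rests on an assumed between-center SD. At SD 0–0.5 there is practically nothing to gain and a small cost. At SD 1.0 the gain is about 1.3–1.8 points of power, and at SD 1.5 about 3–4 points. The larger values need center rates that differ very widely, which the article neither shows nor rules out.

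**What to change.** In Statistical analyses, replace the unstratified primary test with a Cochran-Mantel-Haenszel test stratified by center, and replace the Fisher fallback with the exact stratified version for sparse data. State a rule for pooling centers with very few randomized patients, fixed before unblinding and applied without knowledge of treatment. Report the matching Mantel-Haenszel risk difference with its 95% CI, so that estimate and test use the same strata. The unstratified chi-square can remain as a sensitivity analysis.

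The cost is a few sentences and no extra patients. Trial status reports 16 patients randomized at the time of writing, so at that stage the change could be made on blinded data. The downside is small: centers with evaluable patients in only one arm contribute nothing unless pooled, and if centers do not differ, power falls by about 0.4–0.8 points, or about 1.5 points where lost records leave centers thin. The pooling rule is meant to limit that.
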